### Study visits

The study will consist of an eligibility screening and consent appointment followed by two study visits (see figure 1). At each study visit, participants will undergo clinician-taken cervical screening samples, by an accredited clinician, using a speculum examination and Cervex brush for hrHPV testing and cytology at 6 weeks postnatal. They will also undergo hrHPV testing using first void urine samples collected with a 10 mL Colli-pee device (prior to the clinician-taken sample) at both time points, to ascertain the agreement with clinician-taken sampling and the acceptability to participants at both time points.

**Figure 1 F1:**
[figure not shown]
PINCS-1 participant flowchart. hrHPV, high-risk human papillomavirus; NHS CSP, National Health Service Cervical Screening Programme; NTDD, next test due date; PINCS, Postnatal Instead of Normally-Timed Cervical Screening.

We will perform a patient questionnaire after sampling (web-based or paper), at both 6 weeks and 12 weeks (onlinesupplemental materials 1  2), to ascertain acceptability (concordance with protocol), feasibility (ability to recruit),^29^ patient-reported outcomes, including discomfort of testing, preferences regarding timing of screening and attitudes to introducing the option of screening at the 6 week postnatal check-up in the GP practice. This is based on a questionnaire used in a previous study, following feedback from patients and participants.

### Management of cytology and urine samples

All 6 week cervical samples will undergo initial steps in the laboratory, to allow for safe storage, and saved for processing once the 12 week sample is due. If the participant attends a 6-week sampling but subsequently withdraws from the study prior to 12 weeks, their 6-week sample will be processed and the result will be communicated to them and their GP.

All cervical samples will be processed and tested in the regional cervical cytology laboratory (North Bristol Trust) using the Hologic system. All urine samples will be tested at the cytology laboratory in Manchester using the Roche 8800 platform, as the Hologic system was not as sensitive for urine HPV analysis when compared during a previous study.^27^

Cytology samples performed following a hrHPV positive test will be dual labelled with patient identifying information and study details/study number and stored and managed in accordance with NHS CSP guidance.

Results of the cytological assessment on hrHPV negative samples, which would not ordinarily be performed as part of the NHS CSP, will not be uploaded to the NHS Cervical Screening Administration Service (CSAS), but will be recorded for the purposes of the study and acted on within the study protocol. Cytology samples from hrHPV-negative tests at 6 weeks postnatal will be destroyed at the end of the study period and not made available to CSAS for future audit.

Management of results and further cervical screening will depend on previous cervical screening history (whether up to date at time of study or not), attendance for both samples and results of screening (see figures2  3; online supplemental material 3). The sample that demonstrates the higher-grade abnormality will determine the ongoing pathway, according to NHS CSP management guidelines. Participants will be contacted with results and management plan, questions about further management answered and asked about any adverse events, as well as being encouraged to self-report adverse events to the study team.

**Figure 2 F2:**
[figure not shown]
PINCS-1 study flowchart for those having samples at 6 weeks and 12 weeks. hrHPV, high risk human papillomavirus; NHS CSP, National Health Service Cervical Screening Programme; NTDD, next test due date; PINCS, Postnatal Instead of Normally-Timed Cervical Screening; PROM, patient reported outcome measures.

**Figure 3 F3:**
[figure not shown]
PINCS-1 study flowchart for those having samples at 6 weeks who do not attend for their 12-week sample. hrHPV, high risk human papillomavirus; NHS CSP, National Health Service Cervical Screening Programme; NTDD, next test due date; PINCS, Postnatal Instead of Normally-Timed Cervical Screening.

Urine samples will be labelled with the study details and study ID number and will be destroyed after testing and communication of results with the study team; participants will not be informed of their urine sample results.

### Data collection

Each participant will be assigned a unique study ID following consent to participate. All trial data will be uploaded to the secure web application for managing data, REDCap, which will host the electronic case report form. The study coordinators will be responsible for analysing and monitoring the data from all sites and thus will have full access to the inputted information, and local investigators will be able to access the data from their site only. Participants’ electronic notes and cervical screening records will be accessed up to 1 year after recruitment to gather data on attendance to follow-up, subsequent cervical screening results and any colposcopy assessments.

### Statistical analysis

Full details of the statistical analysis will be described in a statistical analysis plan that will be written and finalised before data lock. The primary acceptability outcomes are binary variables; the number of participants attending at 6 weeks of those who consent and the number attending at both 6 weeks and 12 weeks. We will estimate 95% CIs for each using Wilson’s method. The primary feasibility outcome is the recruitment rate in the substudy of 100 consecutive potential participants. We will compare pain scores on a 10-point scale of testing at 6 weeks and 12 weeks, using paired sample analysis and other patient-reported outcome measures. We will compare inadequacy rates of cytology samples at 6 weeks and 12 weeks. We will use 2×2 tables to analyse sensitivity and specificity of: combination HPV testing and cytology of LBC samples at 6 weeks and 12 weeks; HPV testing of LBC samples versus urine samples at both 6 weeks and 12 weeks.

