There are numerous barriers to screening in young women, including a perception that this age group is not at risk, inadequate knowledge, and fear of pain, discomfort and embarrassment. However, being busy and not getting around to having a test were independent factors, regardless of screening status.^13 14^ Our work showed that we could improve uptake by 8% in the postnatal cohort, largely by improving education of midwives and women in pregnancy.^9^ Detailed quantitative and qualitative feedback in the Attitudes to Postnatal Instead of Normally-Timed Cervical Screening (pre-PINCS) acceptability study^15^ (unpublished data) alongside the previous QI project focus groups told us that new parents have many competing priorities and often struggle to address their own health needs.

National Institute for Health and Care Excellence guidelines recommend a 6-week postnatal check for mothers and babies, which is attended by 78% of eligible people.^16 17^ This appointment provides an opportunity for healthcare professionals to discuss multiple topics: infant feeding, lifestyle advice, contraception and health promotion, including discussion of cervical screening.^17 18^ New mothers and primary care staff told us that offering to combine this visit with postnatal cervical screening would remove a significant barrier, particularly as ‘just putting it off’ was the most common reason for younger women being out-of-date for screening in a study by Jo’s Cervical Cancer Trust.^19^

UK national guidance currently advises waiting 12 weeks after childbirth for a routine cervical screening test if it was due in pregnancy.^20^ This recommendation is based on one comparison of conventional cytology with Papanicolaou smear testing at 4 weeks versus 6 weeks versus 8 weeks postnatal in just 55 participants.^21^ There were increased inflammatory changes in Papanicolaou smears taken earlier, leading to more false-positive, low-grade results. However, this predates hrHPV primary testing (or triage) and liquid-based cytology (LBC), which dramatically improve the ability to test even inflammatory samples and those contaminated by blood and lochia.

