### Study setting

The primary study site will be Somerset NHS Foundation Trust. Two further study sites across South West England will collaborate in this study (Royal Devon and Exeter NHS Trust and Royal Cornwall NHS Foundation Trust), recruiting participants, completing study visits and data collection. Each site is a Gynaecological Cancer Centre. Somerset NHS Foundation Trust acts as the study sponsor. The study planned start date is April 2024 (opened August 2024). Recruitment will end when at least 100 recruited participants have attended and completed clinician-taken cervical screening at their 6-week appointment and have attended or declined to attend their 12-week appointment. If participants withdraw before the 6-week sample, further participants will be recruited, so that at least 100 participants have their 6-week samples performed. The study will end once all participants have completed follow-up, as described above, and data have been collected and analysed. In the instance of low recruitment, an earlier end point may be initiated following discussion with the Independent Trial Steering Committee (ITSC). Anticipated end date is April 2027.

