#### Exclusion criteria

Absence of a cervix.Not eligible for the NHS CSP.Unable to give fully informed consent.

The study is open to all those eligible for cervical screening, regardless of screening status. To understand the reasons for non-participation and to establish an uptake rate, a cohort of 100 potential participants will be approached and the acceptance rate recorded. All those who decline to participate will be given the opportunity to describe the reasons behind this. All participants who initially gave consent to the study but chose to withdraw it will be offered a short electronic questionnaire to identify any concerns and barriers to participation.

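### The paired comparison of pain at 6 and 12 weeks rests on women who return for the second test, and may understate 6-week pain relative to 12 weeks if painful tests deter return

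*Protocol article*

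**What the plan says.** The Statistical analysis section fixes the approach for pain: "We will compare pain scores on a 10-point scale of testing at 6 weeks and 12 weeks, using paired sample analysis". It names no test and does not say what happens to a 6-week score without a 12-week partner. It leaves full analysis details to a statistical analysis plan that is still to be written and is not shown.

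The same article plans for women who do not return. Under Study setting, the recruitment target counts women who "have attended or declined to attend their 12-week appointment", and further women are recruited so that "at least 100 participants have their 6-week samples performed". Participants and recruitment repeats the rule on attending or declining. Figure 3 is captioned "PINCS-1 study flowchart for those having samples at 6 weeks who do not attend for their 12-week sample".

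Pain data do not depend on return. Under Study visits the article says: "We will perform a patient questionnaire after sampling (web-based or paper), at both 6 weeks and 12 weeks". Discomfort of testing is among the items listed there.

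The primary acceptability outcomes are attendance at 6 weeks among those who consent, and "the number attending at both 6 weeks and 12 weeks".

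**The concern.** A woman contributes a within-person difference only if she has both scores, so a plain paired analysis is restricted to women willing to have a second speculum examination. The study treats that willingness as a measure of acceptability in its own right, so the pain comparison would condition on an outcome of interest.

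A link between pain and return is plausible on the article's own account: its Introduction lists "fear of pain, discomfort and embarrassment" among the barriers to screening. If women with more painful 6-week tests return less often, the paired set is short of high 6-week scores. The 6-minus-12-week difference then shifts downward, in favour of 6 weeks, which is the timing under evaluation. At stake is one patient-reported contrast that helps describe how the earlier test is tolerated.

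**Working it through.** **Figures in the plan.** The article gives no SD, expected difference, power or return rate for pain, so there is no stated figure to reproduce.

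**Inputs.**
- From the article: at least 100 women sampled at 6 weeks; a questionnaire after sampling at each visit; non-return permitted.
- Assumed: SD 2.5 points at each visit; within-woman correlation ρ of 0.4 to 0.6; return rate r of 75% or 90%; odds ratio (OR) of return of 1, 0.7 or 0.5 per SD of 6-week pain. OR = 1 means no link.

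**Step 1: an identity that needs no model.** Shortfall in the 6-week mean among returners = (1 − r) × (mean of non-returners − mean of returners).
- Gap 0: shortfall 0 at any return rate.
- Gap 1 point: 0.10 at 90% return, 0.20 at 80%, 0.33 at 67%.
- Gap 2 points: 0.20, 0.40 and 0.66.

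**Step 2: bias in the paired difference.** When the scores are correlated and return depends on 6-week pain, returners' 12-week scores fall too, by ρ times the 6-week shift. So bias in the difference = 6-week shift × (1 − ρ). The 6-week shift comes from bivariate normal scores with logistic return calibrated to r.

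| Return | OR per SD | 6-week shift (points) | Bias in difference, ρ = 0.4 | ρ = 0.6 |
|---|---|---|---|---|
| 75% | 1 | 0 | 0 | 0 |
| 75% | 0.7 | −0.22 | −0.13 | −0.09 |
| 75% | 0.5 | −0.40 | −0.24 | −0.16 |
| 90% | 1 | 0 | 0 | 0 |
| 90% | 0.7 | −0.09 | −0.05 | −0.04 |
| 90% | 0.5 | −0.17 | −0.10 | −0.07 |

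**Step 3: compare with sampling error.** SE of the mean paired difference = SD × √(2(1 − ρ)) / √pairs.
- 75 pairs: 2.5 × √1.2 / √75 = 0.32 at ρ = 0.4, and 2.5 × √0.8 / √75 = 0.26 at ρ = 0.6.
- 90 pairs: 0.29 and 0.24.

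The largest ratio is 0.24 / 0.32, about three-quarters of one SE. At 90% return the largest is 0.10 / 0.29, about a third.

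**Step 4: other assumptions.** With SD 2, a true difference of 1.0, ρ of 0.3 to 0.7 and log-odds slopes of 0.5 or 1 per SD (OR about 0.61 or 0.37), the paired difference at 80% return is 0.76 to 0.94. At 67% return with slope 1 it is 0.61 to 0.83. In that harshest setting, at ρ = 0.3, the bias of 0.39 exceeds the SE of 2 × √1.4 / √67 = 0.29. With slope 0 the difference is 1.0 throughout.

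**Step 5: does using all scores help?** In the Step 2 set-up at 75% return, return depends only on the observed 6-week score. A likelihood-type estimate using every 6-week score cuts the bias to 0.003 points or less.

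**The case against.** The strongest reply is that this is SAP content. The article defers full details, a paired sample analysis is not tied to a complete-case rule, and a mixed model with a participant effect also analyses paired samples. Part of this stands: the unseen SAP may already use the unpaired scores. But the article does more than stay silent. It names an approach whose usual form drops those scores, in a design that expects them.

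Three stronger readings are tempting and are not supported.
- A reader might infer that 6-week pain will be understated. That requires return to fall with 6-week pain. The article names fear of pain only as a general barrier to screening, next to others such as being busy, and gives no figure linking 6-week pain to return.
- A reader might infer that non-returners' scores are thrown away. They are collected, and the secondary objective of evaluating acceptability from questionnaire data is not limited to women with both visits. Women who withdraw consent "will be offered a short electronic questionnaire to identify any concerns and barriers to participation". Any bias is confined to the 6 versus 12 week contrast.
- A reader might infer that this comparison decides whether 6-week screening is acceptable. The primary acceptability outcomes are attendance, and a woman deterred by a painful test counts as a non-attender in the second of them. The Discussion ties progression to study uptake and acceptability of 6-week screening, not to a pain difference.

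It is also fair to say that pain is a secondary measure with no threshold attached, and that every input to the size calculation is assumed.

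**Conclusion.** The point holds in a limited form. On its ordinary reading the stated analysis conditions on return, non-return is expected, and the paired difference may therefore understate 6-week pain relative to 12 weeks. Under the main assumed inputs the bias is 0 to 0.24 points at 75% return and 0 to 0.10 at 90%, less than one SE. It passes one SE only under harsher assumptions, such as two-thirds return with a steep dependence on pain. The lower bound is zero because the article establishes neither the return rate nor any dependence of return on pain. This is a minor improvement to a secondary analysis. It does not touch the primary outcomes.

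**What to change.** In the SAP:
1. Summarise 6-week pain in all women sampled at 6 weeks.
2. Tabulate 6-week pain by whether the woman attended at 12 weeks. This shows directly whether return is related to pain.
3. Estimate the 6 versus 12 week difference with a linear mixed model (visit as fixed effect, participant as random effect) on all available scores, and keep the paired analysis as a sensitivity analysis.

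The cost is SAP wording and a little more analysis, with no new data. The model assumes that 12-week scores are missing at random given 6-week pain. The data cannot verify this, but it is weaker than the assumption behind a returners-only comparison.

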**Trial registration number:**

ISRCTN10071810.

STRENGTHS AND LIMITATIONS OF THIS STUDYTo our knowledge, this is the first study to focus on acceptability and reliability of cervical screening, including urine self-sampling, in postnatal women, to test hypothesis and generate data to inform further study design, following recommendations by Elridge *et al*.There are multiple points at which acceptability will be assessed by collecting participants’ views and participant-reported outcomes.Data collection tools have been developed using participant responses in the Attitudes to Postnatal Instead of Normally-Timed Cervical Screening (pre-PINCS) study, to ensure applicability to the postnatal population.Pilot diagnostic test accuracy data will inform the sample size calculation for future studies.Screening will be performed in secondary care throughout this study, as this study is designed to test the feasibility of a future paired sample diagnostic test accuracy study, not the effect on uptake in a primary care setting; this is a separate question, requiring a different study design.

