#### Secondary objectives

To evaluate the acceptability of clinician-taken cervical samples and self-collected urine samples for screening tests in those who decline, and in those who consent both at 6 weeks and 12 weeks using questionnaire data.To assess the quality of cervical samples from clinician-taken samples at 6 weeks postnatal through inadequacy rates.To determine the agreement in hrHPV status at 6 weeks and 12 weeks postnatal between clinician-taken cervical samples and self-collected urine samples.

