We outline the protocol for a study evaluating the feasibility and acceptability of cervical screening using pair-wise sampling of clinician-taken cervical screening tests and self-sampling with urine samples at 6 weeks and 12 weeks postnatal. Uptake to the study and acceptability of LBC screening at 6 weeks in the consented study sample will inform whether progression to a definitive trial is justified. We will conduct subgroup analyses of uptake based on screening status to determine the feasibility of applying these criteria for the definitive study. To maximise participation in PINCS-1, we will invite women to join regardless of their screening status at the end of pregnancy, since the aim of a subsequent paired-sample study would be to test the DTA of earlier postnatal sampling, not its effect on uptake.

Overall, through the PINCS-1 study and another study (PINCS-2—to test the feasibility of individual randomisation to 6-week vs 12-week study design), we anticipate establishing the level of acceptability and feasibility to inform the design of two further studies and how best to take these forward. First, a DTA study to determine the accuracy of screening for hrHPV and cytological abnormalities at 6 weeks postnatal will be conducted. This will compare the inadequacy rates, sensitivity and specificity of cervical screening at 6 weeks versus 12 weeks postnatal, informing whether offering earlier postnatal screening is accurate. Provisional power calculations, based on inadequacy rates, estimated requiring over 1000 participants for a formal DTA of cervical screening at 6-week postnatal, hence why this feasibility study is required before embarking on such a significant undertaking. Data from PINCS-1 will inform this study design and size for adequate power.

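### Sample-against-sample 2×2 tables are labelled sensitivity and specificity with no reference standard named; they measure agreement, which is the stated objective for urine versus clinician-taken hrHPV

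*Protocol article*

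**What the plan says.** The Statistical analysis section plans 2×2 tables to "analyse sensitivity and specificity of: combination HPV testing and cytology of LBC samples at 6 weeks and 12 weeks". The sentence then adds a second comparison: "HPV testing of LBC samples versus urine samples at both 6 weeks and 12 weeks". It gives no target condition and no reference standard, and does not say which sample serves as the reference. In the first half it does not say what the combined LBC result is tabulated against; the other visit is the natural reading.

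The matching item under Secondary objectives is "To determine the agreement in hrHPV status at 6 weeks and 12 weeks postnatal between clinician-taken cervical samples and self-collected urine samples". Study visits gives the purpose of the urine test in the same terms: "to ascertain the agreement with clinician-taken sampling and the acceptability to participants at both time points". No listed objective covers accuracy or agreement of 6-week against 12-week LBC results; the objective for the 6-week cervical sample is its inadequacy rate.

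Under Management of cytology and urine samples, cervical samples go to one laboratory on the Hologic system, whereas "All urine samples will be tested at the cytology laboratory in Manchester using the Roche 8800 platform". The strengths and limitations box says "Pilot diagnostic test accuracy data will inform the sample size calculation for future studies". The Discussion leaves the formal accuracy comparison to a later study, "estimated requiring over 1000 participants for a formal DTA of cervical screening at 6-week postnatal".

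**The concern.** Sensitivity and specificity are properties of a test against a reference that establishes the target condition. A table crossing two screening samples has no such reference. Errors in whichever sample is treated as the reference, and real change in HPV status over the six weeks between visits, are then charged to the other sample. For urine against LBC, the figure also mixes specimen type with assay platform.

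At stake is how the figures are used. If they are reported as accuracy, the 6-week sample or the urine test may look worse or better than it is, and the figures may enter the design of the later accuracy study as if they were true sensitivity and specificity. The objective actually listed for urine, agreement, would not be answered in its own terms.

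**Working it through.** **Is there a plan figure to reproduce?** No. The article gives no sensitivity, specificity, agreement or prevalence value. Every rate below is an assumption used for illustration.

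**1. Objective against analysis**

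| Comparison | Listed objective | Planned measure |
|---|---|---|
| Urine v LBC hrHPV, each visit | Agreement | Sensitivity, specificity |
| 6-week v 12-week LBC (HPV plus cytology) | None on accuracy or agreement | Sensitivity, specificity |

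The first row is a mismatch. The second is an analysis with no matching objective.

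**2. What one imperfect test shows against another.** Assume prevalence π = 0.12, two tests each with sensitivity Se = 0.95 and specificity Sp = 0.99, and independent errors.

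- Both positive: π·Se² + (1−π)(1−Sp)² = 0.1083 + 0.000088 = 0.1084
- Comparator positive: π·Se + (1−π)(1−Sp) = 0.114 + 0.0088 = 0.1228
- Apparent sensitivity: 0.1084/0.1228 = 88.3%, against a true 95%
- Apparent specificity: 1 − (0.1228 − 0.1084)/0.8772 = 98.4%, against a true 99%

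Varying the inputs: Sp = 0.98 gives 82.6%; π = 0.08 gives 84.8% and π = 0.15 gives 89.7% (both at Sp = 0.99). With weaker tests (Se 0.90, Sp 0.95, π 0.10) apparent sensitivity is (0.081 + 0.00225)/0.135 = 61.7%.

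**3. Dependence of errors.** If the two samples make exactly the same errors, every comparator-positive is also index-positive, and apparent sensitivity and specificity are both 100%. If the comparator is error-free, the true 95% and 99% are recovered. The label can therefore mislead in either direction, or not at all.

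**4. Real change between visits.** In the step 2 model, let a fraction c of infections clear between visits, with the 12-week sample as comparator.

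- c = 10%: both positive = 0.108×0.9025 + 0.012×0.95×0.01 + 0.88×0.0001 = 0.0977; 12-week positive = 0.108×0.95 + 0.892×0.01 = 0.1115
- c = 20%: the same terms give 0.0870 and 0.1002

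| Clearance | P(6-wk+ given 12-wk+) | P(6-wk− given 12-wk−) | P(12-wk+ given 6-wk+) |
|---|---|---|---|
| 0% | 88.3% | 98.4% | 88.3% |
| 10% | 87.6% | 97.2% | 79.5% |
| 20% | 86.7% | 96.0% | 70.8% |

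Apparent 6-week sensitivity moves by less than 2 points. The last column is a different quantity: it would be the sensitivity of the 12-week sample with the 6-week sample as comparator. The same table thus gives quite different figures depending on which sample is called the reference, and the article does not say which.

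**5. Precision.** With about 8 to 15 comparator-positive women in 100, Wilson 95% CIs are 53–98% for 7/8, 65–99% for 11/12 and 70–99% for 14/15.

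**6. The same table, labelled as agreement.** In the step 2 model, positive agreement is 88.3% and negative agreement 98.4%. Overall agreement is 0.1084 + (1 − 2×0.1228 + 0.1084) = 97.1%. Chance agreement is 0.1228² + 0.8772² = 0.7846, so kappa = (0.9712 − 0.7846)/(1 − 0.7846) = 0.87. The arithmetic is unchanged; the interpretation is not.

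**The case against.** The strongest reply is that the defect is only a label. Once a comparator is declared, positive and negative percent agreement are the same proportions from the same table, and the comparator may be declared in the statistical analysis plan, which is not shown. That is right as far as it goes: leaving the choice of comparator to that plan would not be a finding. But the article has already fixed the measure, and for urine it is not the one its own objective and visit description call for.

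A reader might infer that the accuracy figures are bound to be wrong. The document does not support that: steps 2 and 3 show that the result turns on error rates and their dependence, neither of which is given. A reader might also take the 80% and 71% in step 4 as the 6-week sample's sensitivity under clearance; they are not.

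It would also go too far to say that no disease information exists. Data collection provides for later screening results and any colposcopy up to one year. These are not linked to the 2×2 tables, however, and nothing in the article sends a woman to colposcopy on her urine result, so verification would be partial.

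The two platforms are disclosed and the reason is given, so using them is not an error; it only limits what the comparison means. The one sizing basis that the Discussion describes is inadequacy rates, which these tables do not touch. This limits the downstream harm, but does not remove it, because the strengths and limitations box says that the accuracy data will inform later sample sizes.

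**Conclusion.** The point holds as a mismatch between measure and objective. Tables of one sample against another are labelled sensitivity and specificity with no reference named. For urine versus clinician-taken hrHPV, the stated objective is agreement. A reader might extend that objective to 6-week versus 12-week LBC, but it does not cover that comparison, which has no accuracy or agreement objective at all.

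The figures cannot be read as diagnostic accuracy. How far they would depart from it is unknown: about 88% apparent against 95% true sensitivity under the stated assumptions with independent errors, and 100% with fully shared errors. Severity is moderate. The primary outcomes (attendance at 6 weeks, attendance at both visits, and recruitment rate) do not depend on these tables.

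**What to change.** In Statistical analysis, replace sensitivity and specificity with positive, negative and overall percent agreement with 95% CIs, kappa, and the paired difference in positivity. Do this for 6-week versus 12-week LBC, and for urine versus LBC at each visit. Name the comparator in each table. Describe urine versus LBC as agreement between two test systems (urine on Roche, cervical LBC on Hologic).

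Add a secondary objective for agreement of 6-week with 12-week LBC results, so that this analysis has one. In the strengths and limitations box, call the output pilot agreement data rather than diagnostic test accuracy data.

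The cost is wording in the protocol and the statistical analysis plan, which the article says will be finalised before data lock. Samples, visits and tables stay the same.

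### Sensitivity and specificity are planned for the 6- and 12-week cervical samples without a named reference standard; the data collected support agreement, not absolute accuracy

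*Protocol article*

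**What the plan says.** All references are to the protocol article.

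- **Statistical analysis.** The plan is to use 2×2 tables to "analyse sensitivity and specificity of: combination HPV testing and cytology of LBC samples at 6 weeks and 12 weeks". A second table covers "HPV testing of LBC samples versus urine samples at both 6 weeks and 12 weeks". Neither a target condition nor a reference standard is named.
- **Secondary objectives.** None asks for accuracy. One reads "To assess the quality of cervical samples from clinician-taken samples at 6 weeks postnatal through inadequacy rates"; another reads "To determine the agreement in hrHPV status at 6 weeks and 12 weeks postnatal between clinician-taken cervical samples and self-collected urine samples". The Study visits section also speaks of agreement between urine and clinician-taken samples.
- **Data collection.** Notes and screening records are followed up to one year after recruitment for attendance, "subsequent cervical screening results and any colposcopy assessments". These are not linked to the 2×2 tables.
- **Management of cytology and urine samples.** "The sample that demonstrates the higher-grade abnormality will determine the ongoing pathway". Neither time point is treated as the truth.
- **Strengths and limitations box.** "Pilot diagnostic test accuracy data will inform the sample size calculation for future studies". The Discussion adds that PINCS-1 data will inform the design and size of a later accuracy study comparing 6 and 12 weeks.

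**The concern.** Sensitivity and specificity are defined against the true status of each woman. Two sources here could stand in for it, and neither is sufficient.

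The first is the 12-week sample. It is the same screening test, with its own errors, taken six weeks later, when an infection may have cleared or been acquired. It is missing for women who decline the second visit, as the recruitment text allows.

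The second is colposcopy. It is taken from records where it occurred, so women who are not referred have no verified status. Absolute sensitivity and specificity cannot be estimated from that.

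The only cross-classification available for every woman with both samples is 6-week result by 12-week result. Labelling its cells as sensitivity and specificity turns ordinary disagreement between two imperfect tests into apparent inaccuracy of one of them. At stake is what the pilot can conclude and what it hands to the later accuracy study.

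**Working it through.** The plan states no expected sensitivity, specificity or prevalence, so there is no figure of its own to reproduce. The check asks what a 6-week by 12-week table would show if both tests were equally accurate.

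**Assumptions (none from the documents).** Prevalence π = 10%, 15%, 20%. Sensitivity Se = 95% at both visits. Specificity Sp = 97% or 99.5% at both visits. Errors are independent given true status. At first, no change in infection between visits. The model treats the combined result as one positive/negative test.

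**Formula, with 12 weeks as reference.**

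Apparent sensitivity = P(6+,12+) / P(12+) = [π·Se² + (1−π)(1−Sp)²] / [π·Se + (1−π)(1−Sp)]

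| Prevalence | Sp 97% | Sp 99.5% |
|---|---|---|
| 10% | 0.09106 / 0.1220 = 74.6% | 0.09027 / 0.0995 = 90.7% |
| 15% | 0.13614 / 0.1680 = 81.0% | 0.13540 / 0.14675 = 92.3% |
| 20% | 0.18122 / 0.2140 = 84.7% | 0.18052 / 0.1940 = 93.1% |

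For example, at 10% and Sp 97% the numerator is 0.10 × 0.9025 + 0.90 × 0.0009 = 0.09106 and the denominator is 0.10 × 0.95 + 0.90 × 0.03 = 0.1220. True sensitivity is 95% throughout.

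**Swap the roles.** Without turnover, P(6+) = P(12+), so the 12-week test scored against the 6-week sample gets the same figures. The discordant proportions are also equal. At 10% and Sp 97%, each is 0.1220 − 0.09106 = 3.1%, so a symmetric analysis would correctly show no difference.

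**Add turnover.** Suppose 10% of infections clear and 1% of uninfected women become infected.

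- Perfect tests, π = 15%: 0.135 / (0.135 + 0.0085) = 94.1%.
- Perfect tests, π = 10%: 0.090 / (0.090 + 0.009) = 90.9%.
- Perfect tests, π = 10%, clearance only: 0.090 / 0.090 = 100%. Clearance then lowers apparent specificity instead, to 0.90 / 0.91 = 98.9%.
- Se 95%, Sp 97%, π = 15%: P(6+,12+) = 0.135 × 0.9025 + 0.015 × 0.95 × 0.03 + 0.0085 × 0.03 × 0.95 + 0.8415 × 0.0009 = 0.12326, and P(12+) = 0.1435 × 0.95 + 0.8565 × 0.03 = 0.16202, giving 76.1%. With the roles swapped, P(6+) = 0.1680 and the 12-week test gets 0.12326 / 0.1680 = 73.4%.

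In this last case the 12-week test looks the worse of the two. The direction depends on the reference chosen and on the pattern of turnover.

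**Precision.** With 10 to 20 positives in 100 women, Wilson 95% intervals are wide: 9/10 gives 60–98% and 18/20 gives 70–97%.

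**The case against.** The strongest reply has four parts.

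1. **A condensed article defers detail to the analysis plan.** The section says so, and comparator and threshold are the kind of detail that is deferred. This would answer a complaint that the reference is merely unstated. It does not answer the point that nothing collected under this protocol verifies all participants, so an analysis plan cannot make absolute accuracy estimable.

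2. **The article does not say that the 12-week sample is the reference.** This stands. The wording can be read as each time point having its own accuracy, and the Discussion uses similar language for the later study. But that reading then needs an external reference, and partial colposcopy records do not supply one.

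3. **The size depends on undocumented inputs.** This also stands. Moving specificity from 97% to 99.5% shrinks the shortfall markedly, and positively correlated errors (same woman, laboratory and platform) would shrink it further.

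4. **The analysis is secondary.** Primary outcomes are attendance and recruitment, and the Discussion bases its provisional power calculation on inadequacy rates. This stands and limits the weight of the point.

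A reader might go further and infer that no reference of any kind exists, or that a 6-week test as good as the 12-week one is bound to look inferior. The documents support neither. Colposcopy results are collected for some women. The shortfall is symmetric without turnover and can fall on either time point with it. Nor does any passage say that the later study will adopt this figure as its expected sensitivity.

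**Conclusion.** The point holds in a limited form. The Statistical analysis section commits to a quantity that the study's data cannot identify, while the article's own objectives ask for sample quality and agreement. If the table is 6 weeks against 12 weeks, which is an inference, two equally accurate tests would show an apparent sensitivity of about 75–85% (Sp 97%) or 91–93% (Sp 99.5%), given 10–20% prevalence, 95% sensitivity and independent errors. That gap is an artefact of the choice of reference. It says nothing about whether 6-week screening is worse. The correction matters because the figures are described as pilot accuracy data for sizing later studies. It does not touch the primary feasibility and acceptability outcomes.

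**What to change.** - **Statistical analysis, 6- versus 12-week LBC comparison.** Replace sensitivity and specificity with symmetric agreement measures: both discordant proportions (6+/12− and 6−/12+) with a McNemar comparison, overall agreement and kappa, each with a 95% CI. If positive and negative agreement are reported, use the symmetric form or give both directions. Percent agreement against 12 weeks alone would print the same number under another name.
- **Any accuracy measure.** Name the reference (the colposcopy records described under Data collection) and limit reporting to relative detection and relative false-positive ratios among verified women. Label it exploratory, because few women will be verified.
- **Strengths and limitations box.** Describe the pilot output as agreement and discordance data instead of diagnostic test accuracy data.

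The cost is wording and analysis only, on data already being collected. The analysis plan is to be finalised before data lock, so the change can be made there. The one downside is a less ambitious stated deliverable.
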